Our current proposal is based on the 15-16 year follow-up of children enrolled in PROBIT. Our hypotheses build on important findings from a previous follow-up of PROBIT children. In an intention-to-treat analysis, 6.5-year olds in the intervention arm had a 7.5 point advantage in verbal intelligence quotient (IQ) and higher teacher rated reading and writing *vs.* controls. At that age, most children had recently started school, but IQ is sensitive to environmental factors such as length of schooling. Thus, it remains unclear whether breastfeeding has an enduring effect on IQ. Furthermore, the pediatricians administering the IQ tests were not blinded to the children’s randomization status. In our current proposal, we plan to use self-administered tests of cognition and language, which will minimize any administrator bias. Also at age 6.5 years, the PROBIT intervention was not associated with asthma assessed by questionnaire (odds ratio: 1.2; 95% CI: 0.7-1.9), but the wide confidence interval does not exclude potentially important protective or adverse effects. In the current proposal, we include spirometric lung function measures, which index susceptibility to, and consequences of, asthma. Spirometry provides objective and continuous outcome measures, increasing study power. The PROBIT intervention was associated with a reduced risk of atopic eczema at 12 months (odds ratio: 0.54, 95% CI, 0.31-0.95), but was not associated with eczema assessed by questionnaire at 6.5 years (odds ratio: 1.0, 95% CI, 0.5-1.8). However, the reported prevalence of eczema at age 6.5 was also extremely low (1%). We hypothesized that parents may not have reported cases of eczema that were not diagnosed by a doctor. In this proposal, we plan to minimize such underreporting by training the study pediatricians to conduct physical examinations of participant’s skin to identify atopic eczema around the participant’s eyes, neck, elbows, knees or ankles. Such examinations should provide a more systematic approach to identifying true cases of atopic eczema.

Also at age 11.5 years, the PROBIT intervention was not associated with measured obesity (odds ratio: 1.17 (95% CI, 0.97 to 1.41) or blood pressure (mean difference between intervention vs control arms:

1.0 mmHg (95% CI: -1.1 to 3.1) for systolic and 0.8 mmHg (-0.6 to 2.3) for diastolic blood pressure, but the wide confidence interval does not exclude potentially important protective or adverse effects.

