**2.1.2 Atopic eczema**

Breastfeeding is considered an important strategy to prevent the development of atopic eczema and other allergic diseases.^34^ Many allergy organizations, ministries of health, and the World Health Organization recommend between four and six months of exclusive breastfeeding to aid allergy prevention.^34^ These recommendations are largely based on cross-sectional studies.^35,36^ A meta-analysis of 21 observational cohort studies found no convincing evidence for a protective effect of exclusive breastfeeding for at least 3 months on atopic eczema risk up to 4.5 years age^37^, but we are aware of no study that has assessed the impact of prolonged and exclusive breastfeeding on atopic eczema risk during adolescence or later in life.

Methodological shortcomings might explain some of the above contradictions. Observational studies are prone to confounding, in particular due to substantial differences between mothers who do and do not choose to breastfeed, making it difficult to determine whether the observational associations of breastfeeding duration with child health outcomes are causal or have alternative explanations. Observational studies may also be vulnerable to reverse causality, because a mother’s feeding behaviour (whether or not to continue breastfeeding) may be influenced by an infant’s having developed atopic eczema. That may be the reason why some observational studies have found higher atopic eczema risk with longer duration of exclusive breastfeeding.^38^

The PROBIT breastfeeding promotion intervention reduced examination-based atopic eczema incidence in infancy (cluster-adjusted OR, 0.54; 95% CI, 0.31-0.95).^21^ In contrast, no evidence of a protective effect was observed at 6.5 years of age ^50^, but that result was based on questionnaire-based outcomes, rather than physical examination. Relying on questionnaire-derived outcomes for atopic eczema has previously been shown to be inadequate for risk factor analyses, as it attenuates associations; skin examination, using validated diagnostic criteria, is the gold standard, even for large population-based studies.^39^ In this proposal, we will conduct intention-to-treat analysis of PROBIT participants by standardized skin examination, conducted by trained study pediatricians, to provide further experimental evidence on whether increased breastfeeding duration and exclusivity protects against atopic eczema diagnosed over the long term.

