**d. Outcomes in infancy (PROBIT I)**

The first phase of follow-up (PROBIT I) assessed intervention effects on: breastfeeding duration/exclusivity; gastrointestinal and respiratory infection; and atopic eczema among infants.^21^ As seen in **Figure 1**, infants from intervention sites were 7 times more likely to be exclusively breastfed at 3 months (43.3% vs. 6.4%; P<0.001) and 13 times more likely at 6 months (7.9% vs. 0.6%; P = 0.01). Nearly twice as many intervention women were predominantly breastfeeding at 3 months (51.9 vs. 28.3%, p < 0.05) and nearly 7 times as many at 6 months (10.6% vs. 1.6%; P = 0.003). These differences were large enough to cause an appreciable reduction in gastrointestinal tract infections (9.1% vs. 13.2%) and atopic eczema (3.3% vs. 6.3%).

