**b. Exposure, outcomes, and covariates**

The exposure will be randomization to the breastfeeding promotion intervention or to the control group. The expected sample size is 14,000 children from 31 polyclinics.

The main neurocognitive outcomes will be the *Mindstream* scores standardized to an IQ scale (mean 100, SD 15) for memory; executive function; visual-spatial accuracy; verbal function; attention; information processing; motor skills; and a global cognitive score. Vision will be assessed using LogMAR acuity, analyzed as a continuous variable (given its more normal distribution compared to Snellen acuity measures); prevalence of reduced LogMAR visual acuity will also be considered between intervention groups. Atopic eczema outcomes will be evidence of flexural dermatitis around the eyes, the back of the neck, front of the elbows, back of the knees, or ankles, as identified by a trained PROBIT pediatrician; secondary atopic eczema outcomes will include responses to the skin questions from the ISAAC questionnaire. Respiratory function outcomes will be PEFR, FEV_1_ and FVC, each expressed as internal z-scores adjusted for height, age and sex. Adiposity outcomes will be body mass (BMI), fat mass (FMI), and fat-free mass (FFMI) indices, waist-to-height ratio and overweight as BMI between the 85th to <95th percentiles and obesity as BMI at or above the 95th percentile, based on the Centers for Disease Control and Prevention (CDC) 2000 age- and sex-specific reference data. Blood pressure outcomes as continuous measures of systolic and diastolic blood pressure.

Since the number of polyclinics randomized in PROBIT (31) was relatively small, imbalances in baseline covariates sufficient to confound the effect estimates may have occurred. We will therefore conduct a secondary analysis in which we control for any predictors of our outcomes (unadjusted P<0.1) that are also found to be associated (P<0.1) with randomization status. To date, PROBIT analyses suggest that this circumstance is unlikely to occur (see **Table 1**); no evidence of confounding by individual-level covariates was evident in PROBIT I, II or III.^17,21^ The main hospital-level potential confounders are geographic region and urban versus rural location.

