**2.3.6. Power**

Based on follow-up in PROBIT I-III, we expect 14,000 participants in PROBIT IV. We calculated detectable differences based on this number of subjects in 31 clusters, an intention-to-treat (ITT) analysis, 80% power, 5% significance, and used a realistic value (0.01) of the intra-cluster correlation coefficient (ICC) based on the ICCs of outcomes in PROBIT I-III. The effective sample size in PROBIT IV, allowing for the clustered design, is the total number of anticipated participants (14,000) divided by the design effect (*Deff*), where *Deff* = 1+(*n*-1)×ICC and *n* is the average number of individuals per cluster (n=14,000/31=451).^156^ Thus, the design effect for an ICC of 0.01 is 1+4.5=5.5 and the effective sample size is 2,500 children (14,000/5.5). Expected means and SDs for each outcome were taken from childhood cohorts of similar age. Mean detectable differences, assuming exposure groups are dichotomized at the midpoint, are calculated as the product of the SD of each variable and the standardized difference (i.e. 0.1 given an effective sample size of 2,500^157^). For the categorical atopic eczema outcome at the 16-year follow-up (flexural eczema on skin examination), the study has 94% power at the 5% significance level to detect a 50% reduction in atopic eczema prevalence between the two study groups, similar to PROBIT I.^21^

**Table 5** shows the mean differences that can be detected in the comparison of the two randomized arms by ITT and the corresponding effect due to breastfeeding that would have to be present to achieve those ITT differences. The breastfeeding effect is based on the difference in exclusive breastfeeding at 3 months of 43% in the intervention arm and 6% among controls, and is derived by dividing the ITT differences by 0.37=37% (the difference in exclusive breastfeeding in the 2 arms). For comparison, published differences are shown. The sample size is adequate for detecting important differences in the outcomes (**Table 5**). If we fail to find associations in the ITT analysis, the study is powered to have narrow confidence intervals (CIs) around null estimates. The 95% CIs for zero mean differences, assuming an effective sample size of 1250 in each arm ((14,000/Deff) ÷ 2) and means/SDs in Table 2, would be: cognitive score ± 1.2; FEV_1_ ± 40mls; FVC: ± 45mls; PEFR: ± 60mls/s.

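### The 94% power for eczema at age 16 has no stated control prevalence, matches the infancy rates at an ICC of 0.01, and is not supported by the trial's own eczema results

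*Protocol*

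**What the plan says.** Section 2.3.6 (Power) says it "used a realistic value (0.01) of the intra-cluster correlation coefficient (ICC) based on the ICCs of outcomes in PROBIT I-III". It then works out that "the design effect for an ICC of 0.01 is 1+4.5=5.5 and the effective sample size is 2,500 children (14,000/5.5"), and for its interval widths goes on "assuming an effective sample size of 1250 in each arm". The cohort is given in section 2.3.5 b: "The expected sample size is 14,000 children from 31 polyclinics".

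For eczema the section says "the study has 94% power at the 5% significance level to detect a 50% reduction in atopic eczema prevalence between the two study groups", and likens this to PROBIT I. The sentence gives no control prevalence. By contrast, Table 5 lists an expected mean and SD for each continuous outcome.

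The protocol prints eczema results from two earlier phases:

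- **First year of life** (section 2.3.3 d): "atopic eczema (3.3% vs. 6.3"%), intervention against control. Section 2.1.2 gives the effect as "cluster-adjusted OR, 0.54; 95% CI, 0.31-0.95".
- **Age 6.5 years, by questionnaire** (section 1): "the reported prevalence of eczema at age 6.5 was also extremely low (1"%), with an odds ratio of 1.0 (95% CI 0.5-1.8).

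Section 1 suspects that parents under-reported at 6.5 years. Skin examination by trained pediatricians is planned at age 15-16 to reduce this.

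**The concern.** Power for a relative reduction in a proportion depends heavily on the control proportion. Without it, the reader cannot check or interpret 94%. If the figure was carried over from first-year eczema, it describes a different outcome from signs seen at a single examination in adolescence, and nothing in the protocol shows that 6.3% applies at that age.

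The clustering assumption is a second, separate question. The power section uses one ICC of 0.01 throughout, although the trial had already published two cluster-adjusted eczema odds ratios whose intervals show how much clustering this outcome has had.

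Eczema is named in Aim 2 and is the only binary outcome with a stated power. The figure therefore shapes how much weight a null eczema result would be given.

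**Working it through.** **Method.** Two-sided 5% test of two proportions, n effective children per arm, p̄ the mean of p1 and p2:

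power = Φ{ [|p1 − p2| − 1.96·√(2p̄(1−p̄)/n)] / √[(p1(1−p1) + p2(1−p2))/n] }

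n = 7,000 / Deff and Deff = 1 + (m − 1)·ICC, with m = 14,000/31 = 451.6. The protocol does not state sidedness; two-sided is assumed.

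**1. The stated figure.** At n = 1,250:

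- 6.3% vs 3.3% (relative reduction 3.0/6.3 = 48%): (0.030 − 1.96 × 0.00855)/0.00853 = 1.55, power **94.0%**.
- 6.3% vs 3.15% (an exact halving): **96.0%**.
- 5.7% vs 2.85%: 94.1%. Control rates of about 5.3% to 6.2%, halved, fall within two points of 94%.

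The arithmetic therefore reproduces, and the infancy pair is the printed one that matches.

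**2. Clustering implied by PROBIT I.** Inputs: interval 0.31-0.95; 8,181 control and 8,865 experimental infants (Table 1); 6.3% and 3.3%; 31 sites.

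- SE of the log odds ratio: ln(0.95/0.31)/(2 × 1.96) = 0.286; variance 0.0816.
- Variance without clustering: 1/(8,181 × 0.063 × 0.937) + 1/(8,865 × 0.033 × 0.967) = 0.00561.
- Deff = 0.0816/0.00561 = 14.6. With 17,046/31 = 549.9 per site, ICC = 13.56/548.9 = **0.0247**.
- In PROBIT IV: Deff = 1 + 450.6 × 0.0247 = 12.1; n = 7,000/12.1 = **577** per arm.
- Power: 66% for 6.3% vs 3.3%; 71% for a halving. A Wald calculation on the log odds ratio with SE 0.286 gives 66% and 72%.

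Rounding of the published limits moves the two-proportion results to 65-68% and 70-73%. For comparison, an ICC of 0.01 in PROBIT I would give Deff 6.49, SE 0.191 and an interval of about 0.37-0.78, clearly narrower than the one reported.

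**3. Clustering implied by the 6.5-year data.** Inputs: interval 0.5-1.8; 13,889 children (section 2.3.3 e); 1% in each arm.

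- SE: ln(1.8/0.5)/(2 × 1.96) = 0.327; variance 0.1068.
- Variance without clustering: 2/(6,944.5 × 0.01 × 0.99) = 0.0291.
- Deff = 3.67. With 448.0 per site, ICC = 2.67/447.0 = **0.006**.
- In PROBIT IV: Deff = 3.70, n = 1,890 per arm; 1% vs 0.5% gives **43%** (37-51% allowing for rounding of the limits).

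**4. Power for a halving across both unknowns** (unrounded effective sizes):

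| ICC | n per arm | 1% | 2% | 3% | 4% | 6.3% |
|---|---|---|---|---|---|---|
| 0.006 | 1,890 | 43% | 72% | 87.5% | 95% | above 99% |
| 0.01 | 1,271 | 31% | 55% | 72% | 84% | 96% |
| 0.025 | 571 | 16% | 28% | 40% | 51% | 71% |

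**The case against.** **It is not an arithmetic error.** This stands. The 94% reproduces; what is in dispute is its inputs. The reference to PROBIT I also partly discloses their source. A reader might infer that the infancy rates are the only possible source, but halving a control rate near 5.7% gives the same figure.

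**The 1% is not a planning value.** This also stands. It is a questionnaire figure. Section 1 suspects under-reporting, section 2.1.2 treats skin examination as the gold standard, and section 2.3.4 b counts signs at any of five sites. It can serve only as a pessimistic bound.

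**The two phases disagree about clustering.** PROBIT I points above 0.01 and the 6.5-year data point below it, so 0.025 cannot simply replace 0.01. Both ICCs are also back-calculated, assuming normal-quantile intervals and equal cluster sizes. Two stronger readings fail here. A reader might infer that power is really about 16%, but that joins the 6.5-year prevalence to the infancy ICC; 1% alone at ICC 0.01 gives 31%, and PROBIT I precision alone gives 66-72%. A reader might equally infer that 94% is unattainable, but an ICC of 0.006 with a control prevalence of 4% gives 95%. The documents establish no age-16 prevalence that would settle either.

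**No decision depends on it.** Largely right. The sample is the whole existing cohort, section 2.3.5 c commits to 95% intervals, and section 1 already reads earlier null results by their intervals. It does not rescue the figure: the interval widths worked out in section 2.3.6 for null results cover continuous outcomes only.

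**Conclusion.** Wrong as written, because a single 94% is stated without the prevalence it needs and without support from the trial's own eczema data. Each phase, with its own prevalence and its own clustering, gives clearly less: about 66-72% from infancy and about 43% from age 6.5 years, the latter a pessimistic bound. What is shown is that the claim is unsupported, not that the true power is any one lower value.

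The conclusion rests on a two-sided test, on 14,000 children in 31 roughly equal clusters, and on ICCs recovered from rounded published intervals. Rounding moves the results by a few points in infancy and by about seven points either way at 6.5 years, which does not change the conclusion.

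The point should be corrected but is not critical: the cohort is fixed, so the sentence affects interpretation and not the design or the sample size.

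**What to change.** In section 2.3.6, replace the 94% sentence with three things:

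1. The control prevalence assumed for flexural eczema at age 15-16, and the reason for it.
2. A table of power for a halving over control prevalences of about 1% to 6% and eczema ICCs of about 0.006 to 0.025, with both earlier phases named as the sources of that range. The table above can serve as a start.
3. A sentence saying that a null eczema result will be interpreted from its confidence interval.

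The cost is one recalculation and a reworded sentence, with no change to data collection or analysis. The downside is that the stated power becomes a range, most of it less favourable than 94%.

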***Table 5:* *Expected control group means, SDs, and differences detectable (alpha= 0.05, 80% Power)***

| **Continuous Outcomes** | **Mean** | **SD** | **Mean detectable differences: ITT** | **Breastfeeding effect to produce detectable effect** | **Differences observed in other studies** |
| --- | --- | --- | --- | --- | --- |
| Global cognitive score | 100 | 15 | 1.5 | 4.1 | 2-5^16^ |
| FEV_1_ (mls)^a^ | 3345 | 480 | 48 | 130 | 40^59^ |
| FVC (mls)^a^ | 3700 | 575 | 58 | 150 | 54-103^58,59^ |
| PEFR (mls/s)^a^ | 6200 | 800 | 80 | 200 | 180^4,59^ |
| LogMar visual acuity | 0.02^b^ | 0.2^b^ | 0.02 | 0.05 | 0.05^5-7,101,158^ |
| Systolic blood pressure (mmHg)^159^ | 99.9 | 9.6 | 1.15 | 3.11 | Meta-analysis: 1.4 Max difference: 6.5^160^ |
| Diastolic blood pressure (mmHg)^159^ | 57.0 | 6.8 | 0.82 | 2.22 | Meta-analysis: 0.5; Max differences: 3.4^161,162^ |
| Body mass index (kg/m^2^) ^c^ | 16.2 | 2.0 | 0.024 | 0.06 | 0.4^163^; 0.28-0.57^72,164^ |

^a^Data from ALSPAC, standardized for height; ^b^Northern Ireland Childhood Errors of Refraction study (personal communication); ^c^Estimates of means and SDs obtained from ALSPAC.

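### Table 5 does not support the statement that the sample size is adequate for lung function or for the meta-analytic blood pressure differences

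*Protocol*

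**What the plan says.** Section 2.3.6 of the protocol states that "we expect 14,000 participants in PROBIT IV" and sets "80% power, 5% significance" as the basis for the detectable differences. Section 2.3.5b gives the cluster count: "The expected sample size is 14,000 children from 31 polyclinics". With an ICC of 0.01, the section derives a design effect of 5.5, an effective sample size of 2,500 (1,250 per arm) and a detectable standardized difference of 0.1.

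Table 5 then shows, for each outcome, the detectable intention-to-treat (ITT) difference, the breastfeeding effect needed to produce it (ITT difference divided by 0.37, the between-arm gap in exclusive breastfeeding at 3 months), and published differences for comparison. From this the section concludes: "The sample size is adequate for detecting important differences in the outcomes".

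Three of the rows, in the order mean, SD, ITT difference, required breastfeeding effect, published difference:
- FEV1: "3345 | 480 | 48 | 130 | 40"
- FVC: "3700 | 575 | 58 | 150 | 54-103"
- Systolic blood pressure: "99.9 | 9.6 | 1.15 | 3.11 | Meta-analysis: 1.4", followed in the same cell by a maximum difference of 6.5.

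**The concern.** The last two columns of Table 5 are on the same scale: what breastfeeding would have to do, and what other studies report that it does. For lung function and for pooled blood pressure the first is larger than the second, so the table the conclusion cites does not lead to it.

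Lung function belongs to Aim 2 and blood pressure to Aim 3. Section 2.3.8 also credits the large sample with limiting type 2 error for effects of public health importance, and the protocol expects its results to inform policy. A null ITT result for FEV1 or blood pressure, read under that assurance, could be taken as evidence against effects of the published size when the trial had little chance of detecting them.

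**Working it through.** **Inputs.** From 2.3.6: N = 14,000, 31 clusters, ICC 0.01, 5% significance, 80% power, scaling factor 0.37. From Table 5: SDs, ITT differences, required effects and published differences. The test is taken as two-sided because 2.3.5c specifies 95% confidence intervals and Wald tests.

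**1. The protocol's effective sample size.** Mean cluster size 14,000/31 = 451.6. Design effect 1 + 450.6 × 0.01 = 5.506. Effective N = 14,000/5.506 = 2,543, which the protocol rounds to 2,500. This reproduces.

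**2. The 0.1 SD figure.** The standard error of a standardized difference with 1,250 per arm is √(2/1250) = 0.04. Two-sided 5% with 80% power needs (1.960 + 0.842) × 0.04 = 0.112 SD. One-sided 5% gives (1.645 + 0.842) × 0.04 = 0.099. At 0.1 SD, two-sided power is 70.5%. The table is therefore slightly optimistic wherever 0.1 is used. The blood pressure rows use about 0.12 (1.15/9.6 and 0.82/6.8).

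**3. Required breastfeeding effect = ITT difference / 0.37.**

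| Outcome | ITT / 0.37 | Printed | Published | Printed ÷ published |
|---|---|---|---|---|
| FEV1 (mL) | 48/0.37 = 130 | 130 | 40 | 3.25 |
| FVC (mL) | 58/0.37 = 157 | 150 | 54-103 | 1.46-2.78 |
| PEFR (mL/s) | 80/0.37 = 216 | 200 | 180 | 1.11 |
| Systolic BP (mmHg) | 1.15/0.37 = 3.11 | 3.11 | meta-analysis 1.4 (max 6.5) | 2.22 (against 1.4) |
| Diastolic BP (mmHg) | 0.82/0.37 = 2.22 | 2.22 | meta-analysis 0.5 (max 3.4) | 4.44 (against 0.5) |

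The FVC and PEFR entries are printed too low. With 0.112 SD in every row, the required effects become 145, 174, 242, 2.91 and 2.06. Each still exceeds the lung or meta-analytic comparator.

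**4. Power at the published difference.** z = (published × 0.37)/(0.04 × SD); power ≈ Φ(z − 1.96).
- FEV1: 14.8/19.2 = 0.77, power 12%.
- FVC: 20.0/23 = 0.87 and 38.1/23 = 1.66, power 14% and 38%.
- PEFR: 66.6/32 = 2.08, power 55%.
- Systolic: 0.518/0.384 = 1.35, power 27%.
- Diastolic: 0.185/0.272 = 0.68, power 10%.
- For contrast, cognition: 2 points gives 23% and 5 points 87%. Power of 80% is reached at 0.112 × 15/0.37, about 4.5 points. Visual acuity at its published 0.05 gives 64%.

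**5. Maximum blood pressure differences.** At ICC 0.01, power for 6.5 and 3.4 mmHg exceeds 99%. Table 4, however, gives systolic pressure an ICC of 0.12. The design effect is then 1 + 450.6 × 0.12 = 55.1, effective N is about 254, and the SE is 9.6 × √(2/127) = 1.20. For 6.5 × 0.37 = 2.405 mmHg, z = 2.00 and power is about 51%.

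**The case against.** **The word important is not defined, and the protocol does not adopt the published values as targets.** Sections 2.1 and 2.1.4 call such observational evidence prone to confounding and publication bias. This stands as far as it goes: the sentence is not an arithmetic contradiction. But it cites Table 5, and the published column is the only benchmark there, so the table does not support it for these outcomes.

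**A reader might infer that Table 5 shows inadequacy for most outcomes.** The documents do not support that.
- Cognition (4.1) lies within 2-5, and acuity (0.05) equals its comparator.
- Blood pressure lies between its two printed comparators, so the shortfall is against the meta-analyses only.
- BMI as printed (0.06 against 0.28-0.57) shows no shortfall. One appears only after a separate error is corrected: 0.024 is printed where 0.1 × 2.0 gives 0.2.

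Only the three lung rows lie beyond every printed comparator, and PEFR only modestly.

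**The power figures depend on the 0.37 scaling.** They assume that each published difference measures the same contrast as exclusive breastfeeding at 3 months. Table 5 does not define those exposures, and the intervention also shifted predominant breastfeeding (51.9% against 28.3% at 3 months). This stands, so the percentages are conditional. The scaling is nevertheless the protocol's own.

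**The section already plans to read nulls from confidence intervals.** It gives ITT half-widths of 40 mL for FEV1, 45 mL for FVC and 60 mL/s for PEFR. Divided by 0.37 these are about 108, 122 and 162. An exactly null estimate would not exclude the published FEV1 or FVC differences; it would narrowly exclude 180 for PEFR. No half-widths are given for blood pressure.

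**The cohort is fixed, so nothing operational changes.** True. This limits the point to what is claimed and how null results are read.

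**Conclusion.** The adequacy statement is not supported by Table 5 for FEV1, FVC, PEFR or the meta-analytic blood pressure differences. The required effects are about 1.1 to 4.4 times the published values as printed. Power at the published values runs from about 10% to 55%, given an ICC of 0.01, 1,250 effective participants per arm, a two-sided 5% test and the 0.37 scaling. An ICC above 0.01 would lower it.

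Two further inferences should be avoided. The table does not show a shortfall for most outcomes. Nor does the high power for the maximum blood pressure differences at ICC 0.01 establish adequacy there: at the systolic ICC in Table 4, it falls to about 51% for 6.5 mmHg.

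**What to change.** In section 2.3.6 and Table 5:

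1. Replace the adequacy sentence with an outcome-by-outcome statement: at ICC 0.01 and under the 0.37 scaling, 80% power is reached only for cognitive effects of about 4.5 points or more. It is not reached for the published FEV1, FVC and PEFR differences or the meta-analytic blood pressure differences.
2. Correct the required breastfeeding effect to 157 for FVC and 216 for PEFR.
3. Add a column of power at the published difference, labelled as conditional on the 0.37 scaling.
4. Make no adequacy claim for the maximum blood pressure differences unless it is recomputed at the trial's own blood pressure ICC (0.12 for systolic in Table 4).
5. State that null lung and blood pressure results will be read from the confidence interval on the breastfeeding-effect scale, and add blood pressure half-widths. At ICC 0.01 these are 1.96 × 0.04 × 9.6/0.37 = 2.0 mmHg systolic and 1.96 × 0.04 × 6.8/0.37 = 1.4 mmHg diastolic. They should also be shown at the trial's own ICC.
6. Handle the BMI entry (0.024 against 0.2) as a separate correction.

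The cost is a few sentences, two table cells and one column. No data collection or analysis changes; the power claim becomes less favourable.
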